### Intervention

The intervention to be tested is predominant fluid resuscitation with balanced/buffered fluids (LR, Hartmann’s, or PlasmaLyte, as per local site preference) compared to the “usual practice” of predominant 0.9% saline resuscitation. Other than prescribing which crystalloid fluid type to use, the intervention will be implemented without efforts to standardize timing and volume of fluid resuscitation or other components of clinical care. Thus, all decisions to administer fluid, as well as timing, volume, and rate of fluid administration, remain at the discretion of the treating clinicians. Hospital fluid supplies will be used for this study without any change to packaging or labeling. Participants will be randomized to receive either balanced/buffered fluids or 0.9% saline for all bolus and maintenance fluid administration starting from randomization through 11:59 pm on the following calendar day. Maintenance fluids are included because these constitute a substantial proportion of total crystalloid fluid administration [35], including 40% of total crystalloids as maintenance fluids in our pilot study [25]. If the treating clinician deems it unsafe to continue study fluid or identifies a clinical indication that requires specific fluid or electrolyte therapy (e.g., hyponatremia, hyperkalemia, hypercalcemia, cerebral edema), non-study fluids are permitted. Use of non-isotonic fluids (e.g., 0.45% saline) is not recommended as standard maintenance fluids in children [36] and will be discouraged during the intervention phase. Colloid fluids and blood products may be administered at the discretion of the treating team.

Ending the intervention phase at 11:59 PM on the calendar day following randomization ensures all participants are eligible to receive study fluid for a minimum of 24 and a maximum of 48 h. This represents the time-window from the presentation during which most fluid resuscitation is completed for septic shock [17] and provides a pragmatic endpoint that signals the end of the intervention phase.

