### Adherence

All fluid administered through the end of the intervention window will be recorded. Adherence to the intervention is defined as receipt of ≥75% of total crystalloid fluid as the randomized fluid type during the interventional window. For example, participants randomized to balanced/buffered fluids are considered adherent to the intervention if they receive ≥75% of their total crystalloid as balanced/buffered fluids starting from the time of randomization through 11:59 PM on the following calendar day. Locally, all sites will establish a work-flow to communicate study enrollment and promote adherence across providers and hospital locations. Such strategies include verbal and/or written hand-offs between providers, use of a templated orderset indicating PRoMPT BOLUS study enrollment and treatment allocation, and automated electronic reminders to clinicians at the time an order is placed for non-study crystalloid fluids during the intervention window. Each participant’s adherence to the intervention will be monitored centrally, and the mean adherence to the intervention for all participants within each site will be regularly reported back to local investigators. Targeted education will be undertaken if < 80% of participants in either study arm meet the adherence criterion. If < 70% of participants meet the adherence criterion over two consecutive months, the site will be placed on monitored probation with additional efforts undertaken to understand and correct challenges to adherence. Sites that continue to fail to meet the adherence threshold in at least 80% of enrolled participants may be removed from study participation.

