### Outcomes

The primary outcome will be MAKE30—a composite of death from any cause, initiation of RRT, or persistent kidney dysfunction—at either 30 days following study enrollment or hospital discharge, whichever comes first (Table 2) [38]. RRT will include treatment (or attempt to treat if the participant does not tolerate treatment) with any renal replacement modality during the hospitalization that was not a continuation of pre-hospital chronic therapy, censored at 30 days after randomization. Persistent kidney dysfunction will be measured as final creatinine ≥200% of baseline (i.e., at least a doubling of baseline creatinine) *and* a minimum absolute increase of ≥0.3 mg/dL. Baseline serum creatinine will be recorded as the lowest creatinine available between 12 months and 24 h prior to enrollment or, for participants without such data, an imputed value using established median values for age and sex [39]. Secondary efficacy, safety, and biologic outcomes are listed in Table 2.

**Table 2 Tab2:** Study outcomes

Outcome	Definition
Primary outcome	
MAKE30 (primary outcome)	Major adverse kidney events at 30 days (defined as at least one of the following): • Death • New renal replacement therapy • Persistent kidney dysfunction at hospital discharge or 30 days (serum creatinine ≥2x baseline or median value for age if no baseline available *and* a minimum absolute increase of ≥0.3 mg/dL)
Secondary effectiveness outcomes	
Death	All-cause mortality at hospital discharge, 28 days, and 90 days^b^
Hospital length of stay	Days from hospital admission until discharge, censored at 90 days
Hospital-free days out of 28 days	Days between enrollment and day 28 in which patient was alive and out of the hospital
New inpatient renal replacement therapy	New continuous renal replacement therapy, hemodialysis, or peritoneal dialysis
Persistent kidney dysfunction at hospital discharge	Serum creatinine ≥2x baseline or median value for age if no baseline^a^ available, censored at 30 days
Secondary safety outcomes^c^	
Hyperlactatemia	> 4 mMol/L
Hyperkalemia	> 6 mEq/L
Hypercalcemia	Ionized calcium > 1.35 mmol/L or total serum calcium > 12 mg/dL
Hypernatremia	> 155 mEq/L
Hyponatremia	< 128 mEq/L
Hyperchloremia	> 110 mEq/L
Thrombosis	Therapy for new arterial or venous thrombus with systemic anticoagulant OR Clotting of intravenous catheter in subjects receiving ceftriaxone and lactated Ringer’s

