Cerebral edema	Therapy with hyperosmolar therapy (hypertonic saline and/or mannitol) for radiographic and clinical determination of new impending or present brain herniation
Secondary biologic outcomes^d^	
Urine neutrophil gelatinase-associated lipocalin	Biomarkers will be measured on the day of randomization (day 0), day 2, and day 27 (or prior to death or anticipated discharge, whichever comes first). Analyses will include between-group differences in absolute biomarker values at each timepoint and, to account for potential baseline differences, the percent change in biomarkers relative to measurements on study 0.
Urine kidney injury molecular-1	
Urine liver-type fatty acid-binding protein	
Urine interleukin-18	
Plasma cystatin C	

^a^Baseline creatinine will be determined for each study participant as the lowest recorded creatinine available between 12 months and 24 h prior to the index admission. For participants without such data available, an estimated baseline creatinine will be imputed using previously established median values for age and sex

^b^Mortality at 90 days will be measured using vital status obtained from the medical record at all sites, as well as the US National Death Index and Canadian provincial vital statistics if vital status cannot be confirmed using medical records alone

^c^Safety outcomes must occur within 4 calendar days of randomization, except thrombosis which must occur within 7 days of randomization

^d^Plasma and urine biomarkers of kidney injury will also be collected from study participants enrolled at a subset of sites

The rationale for MAKE30 as the primary endpoint is that mediation of kidney injury provides the major mechanistic pathway through which balanced/buffered fluids are likely to improve patient outcomes. In addition, the only prior comparable randomized clinical trials demonstrated a reduction in MAKE30 with the use of balanced/buffered fluids in adult patients with sepsis [17, 18]. Finally, MAKE30 provides an objective and easily measured outcome endorsed as a patient-centered endpoint for clinical trials [40].

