### Adverse events

Adverse events (AEs) will be queried from the medical record at the end of the intervention phase and between study days 5–7. We will limit the time period for the determination of AEs because we are unaware of any biologically plausible reason to anticipate that either fluid type should lead to AEs remote from the immediate intervention period. AEs that are unexpected, serious, and at least possibly related to study fluid type will be reviewed by the international steering committee and reported promptly to regulatory bodies.

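### The thrombosis safety outcome counts a clotted IV catheter only in children given ceftriaxone and lactated Ringer's, so one limb of a between-arm comparison depends on the randomized fluid

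*Protocol article*

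**What the plan says.** Table 2 (Outcomes) gives thrombosis two limbs joined by OR. The first is a new thrombus, arterial or venous, that is treated with systemic anticoagulation. The second is "Clotting of intravenous catheter in subjects receiving ceftriaxone and lactated" Ringer's. Footnote c to that table sets the time limits: "Safety outcomes must occur within 4 calendar days of randomization, except thrombosis which must occur within 7 days of randomization".

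The Intervention section describes the tested strategy as "predominant fluid resuscitation with balanced/buffered fluids (LR, Hartmann’s, or PlasmaLyte, as per local site preference"), "compared to the “usual practice” of predominant 0.9% saline resuscitation". It also says that, where the clinician judges study fluid unsafe or sees a specific indication, "non-study fluids are permitted". The Adherence section defines adherence as "receipt of ≥75% of total crystalloid fluid as the randomized fluid type during the interventional window".

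Statistical analysis states that secondary outcomes are analyzed by intention to treat with Benjamini-Hochberg control, and refers to Additional file 4 (not shown) for the detail. Presentation of the results says that all outcomes are reported by treatment group. The Background makes relative safety a secondary aim and hypothesizes no increase in adverse effects with balanced fluid. Nothing in the article says that the catheter limb is descriptive, or that it is kept out of the comparison.

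**The concern.** A between-arm comparison needs a case definition that does not refer to the treatment. The first limb meets this: a treated new thrombus counts whatever the fluid. The second does not, because receipt of LR is part of the definition of an event and LR belongs to one arm's fluid class.

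Two consequences follow. First, if fluid type has no effect on clotting, the composite still records more events in whichever arm received more LR, which by design should be the balanced arm. Second, if ceftriaxone with LR really does clot catheters, the composite cannot show it, because children on ceftriaxone without LR have no recorded clotting rate to compare with. Either way, an excess of thrombosis in the balanced arm would be hard to interpret, in a trial whose safety hypothesis is that no such excess exists. Intention-to-treat analysis and multiplicity control do not repair a definition that differs by arm.

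**Working it through.** **Which children can contribute a catheter event.** Reading Table 2 against the fluids named under Intervention, for a child whose catheter clots:

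| Fluids received | With ceftriaxone | Without ceftriaxone |
|---|---|---|
| Any LR (either arm) | counts | does not count |
| Saline only | does not count | does not count |
| PlasmaLyte or Hartmann's, no LR | does not count | does not count |

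The asymmetry between arms therefore depends on the difference in LR exposure, and varies by site because the choice of balanced fluid is local.

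**Size.** The plan states no thrombosis rate or power, so there is no figure to reproduce. The following is illustration only. The one input from the article is 8800 participants allocated equally, so 8800 / 2 = 4400 per arm. The other inputs are assumptions, with *t*, *q* and *f* the same in both arms:

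- *t*: risk of treated new thrombus
- *q*: risk of catheter clotting
- *f*: share given ceftriaxone
- *L*: share of the arm receiving any LR

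Taking these as independent, the recorded risk in an arm is

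*p* = 1 − (1 − *t*)(1 − *f·L·q*) = *t* + (1 − *t*)·*f·L·q*.

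Worked case: *t* = 1%, *q* = 2%, *f* = 50%, LR in 50% of the balanced arm and 25% of the saline arm.

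- Balanced: 0.01 + 0.99 × 0.5 × 0.50 × 0.02 = 0.01495
- Saline: 0.01 + 0.99 × 0.5 × 0.25 × 0.02 = 0.01248
- Spurious RR = 0.01495 / 0.01248 = 1.20

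The last column below is the chance that a two-proportion test (two-sided 0.05, before Benjamini-Hochberg) shows a significant excess in the balanced arm. Without the bias it would be 2.5%.

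| *t* | *q* | *f* | LR balanced / saline | Recorded risk, balanced vs saline | RR | Chance of false excess |
|---|---|---|---|---|---|---|
| 1% | 1% | 30% | 50% / 25% | 1.15% vs 1.07% | 1.07 | 5% |
| 1% | 2% | 50% | 50% / 25% | 1.50% vs 1.25% | 1.20 | 17% |
| 0.5% | 1% | 30% | 90% / 10% | 0.77% vs 0.53% | 1.45 | 29% |
| 1% | 2% | 50% | 90% / 5% | 1.89% vs 1.05% | 1.80 | 91% |
| 0.5% | 3% | 60% | 90% / 10% | 2.11% vs 0.68% | 3.11 | above 99% |

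More extreme inputs go further: *t* = 0.5%, *q* = 5%, *f* = 60%, LR 90% / 0% gives 3.19% vs 0.50%, RR 6.37.

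**What drives it.** The difference in recorded risk is (1 − *t*)·*f·q*·(*L* balanced − *L* saline). It is positive whenever LR use is higher in the balanced arm and zero only if LR use is equal.

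**After the fix.** Under a rule that ignores fluid, *L* drops out and equal true risks give equal recorded risks. For example, counting clotting in any child on ceftriaxone, with *t* = 0.5%, *q* = 1%, *f* = 30%, gives 0.005 + 0.995 × 0.003 = 0.80% in both arms, RR 1.00.

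**The case against.** The strongest reply is that saline-arm children can be exposed to LR, so the limb is not closed to them. Table 2 sets no timing or volume for LR. Participants allows up to 40 mL/kg of crystalloid before enrollment. Adherence is a share of volume, so an adherent saline child may receive up to 25% as other fluid. The intervention ends at 24 to 48 hours, while thrombosis counts to day 7. All of this stands. It rules out saying that a saline child's clotted catheter can never count, and the 75% threshold does not cap the proportion of saline children exposed to LR. It shrinks the bias but does not remove it unless LR exposure is equal in the two arms, which would defeat the randomized contrast at sites using LR.

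It is also fair that the size rests wholly on assumptions, that sites using PlasmaLyte or Hartmann's contribute little asymmetry, that Benjamini-Hochberg control would lower the chances of significance shown, and that Additional files 3 and 4 may collect or report the limbs separately. The printed definition is nevertheless the one given for the outcome.

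A reader might infer more than the article supports:

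- **Intent.** The wording reads as monitoring of a particular drug-fluid combination, not as an attempt to produce a result.
- **No usable comparison.** The anticoagulant-treated limb is symmetric and can be compared as it stands.
- **Truncated follow-up.** Adverse events "will be queried from the medical record at the end of the intervention phase and between study days" 5–7, which might seem to miss part of a 7-day window. The article does not make that query the only way thrombosis is found, and the schedule is the same in both arms.
- **Pre-existing laboratory values counted as events.** Table 2 does not call these outcomes new, but footnote c can be read as requiring onset after randomization, and a condensed article may leave such handling to the full protocol.

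**Conclusion.** The point holds in a limited form. The catheter limb depends on the randomized treatment, so the thrombosis composite is biased towards more events with balanced fluid whenever LR use is higher in that arm. The direction follows from the definition and that one condition. The size cannot be known from the documents: with equal true risks, the assumed inputs give a spurious RR from about 1.07 to above 3, and the chance of a falsely significant excess runs from slightly above nominal to near certainty. No single value deserves emphasis.

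The consequence is confined to one secondary safety outcome. MAKE30, the sample size and the interim monitoring are unaffected, and the artefact cannot make balanced fluid look safer than it is. This is a worthwhile and inexpensive correction to an outcome definition, not a threat to the trial's main conclusion.

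**What to change.** Use anticoagulant-treated new thrombus alone as the thrombosis outcome compared between arms. Record catheter clotting by the same rule in every participant, whatever the fluid or antibiotic, and report it by arm as its own item. Keep clotting in children given both ceftriaxone and LR as a descriptive listing, which preserves the monitoring purpose without entering the comparison. If Additional file 4 already separates the limbs, Table 2 should say so.

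The cost is a wording change and one unrestricted catheter-clotting field. Ceftriaxone use and crystalloid volumes are already due to be tabulated by arm (Tables 3 and 4). Children already enrolled would need chart review for catheter clotting, or could be reported on the anticoagulant-treated limb only, in which case the separate catheter item covers later enrollees alone.

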### Consent

Prospective written informed consent will be sought from a legally authorized representative (LAR, e.g., at least one parent) prior to enrollment *when sufficient time permits*. However, because of the life-threatening nature of septic shock and narrow therapeutic window to commence fluid resuscitation, enrollment may proceed in the USA under the federal “Exception From Informed Consent” (EFIC, 21 CFR 50.24) for emergency research [26] and in Canada and Australia/New Zealand with “deferred consent” in compliance with the Canadian Tri-Council Policy Statement-2 [27] and National Statement on Ethical Conduct in Human Research [28], respectively. Such enrollment methods are ethically suitable for emergent, life-threatening conditions when patients may benefit from the research, available treatments are unproven/unsatisfactory, and obtaining prospective informed consent is not feasible [25, 29–32]. A waiver of assent will be requested due to the critical nature of illness in septic shock.

To comply with federal and ethical guidelines, community consultation and public disclosure were conducted in the USA (available at https://www.regulations.gov/docket/FDA-1995-S-0036) and community consultation was conducted in Australia/New Zealand to obtain input from and inform the local community prior to beginning enrollment [33, 34]. All EFIC studies are also subject to additional regulation through the US FDA, which approved the study protocol under an Investigational New Drug (IND #136978) application.

Participants enrolled under EFIC (USA) or deferred consent (Canada, Australia/New Zealand) will be notified of enrollment and study procedures as soon as feasible and offered the right to withdraw from or continue in the study. For study participants who die prior to the post-enrollment discussion in the USA or deferred consent in Canada or Australia/New Zealand, all reasonable attempts will be made to inform the LAR after the participant’s death, unless a waiver has been granted in local jurisdictions. However, successful LAR contact will not be required to include data in the analysis. At a subset of sites collecting biological samples, separate written informed consent will be obtained for the measurement of blood and urine biomarkers.

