### Subgroup analyses

We will evaluate treatment differences among subgroups defined by the following stratification variables: age group, sex, cancer comorbidity, AKI at study enrollment, abnormal kidney function using day 0 biomarker measurements (Table 2), total fluid volume received during intervention window, and country of enrollment. If there is significant heterogeneity in treatment effect using the Breslow-Day test [45], we will report separate results within strata.

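### The last biomarker sample is compared between arms as one timepoint, although it is taken at discharge, death or day 27, and discharge and death may depend on fluid type

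*Protocol article*

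**What the plan says.** The Background gives the effect of fluid type on kidney injury biomarkers as a secondary aim. The biomarkers are four urine markers and plasma cystatin C, collected at a subset of sites (Outcomes, Table 2 and its notes).

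- **Sampling times (Table 2).** For the first sample: "Biomarkers will be measured on the day of randomization (day 0"). The two later samples are set for "day 2, and day 27 (or prior to death or anticipated discharge, whichever comes first").
- **Planned contrasts (Table 2).** The first is on the raw scale: "Analyses will include between-group differences in absolute biomarker values at each timepoint". The second is meant as a baseline adjustment: "to account for potential baseline differences, the percent change in biomarkers relative to measurements on study 0".
- **Discharge and death as outcomes (Table 2).** Length of stay, hospital-free days to day 28 and mortality are secondary effectiveness outcomes. The Sample size section quotes power for a 1-day difference in hospital-free days and for mortality of 3% versus 2%.
- **Blinding.** Participants, clinicians and investigators know the allocation.
- **Study fluid (Intervention).** It is given "for all bolus and maintenance fluid administration starting from randomization through 11:59 pm on the following calendar day".
- **Consent.** At the biomarker sites, "separate written informed consent will be obtained for the measurement of blood and urine biomarkers". Children enrolled ahead of consent, through their families, "will be notified of enrollment and study procedures as soon as feasible and offered the right to withdraw".
- **Subgroup analyses.** One subgroup factor is "abnormal kidney function using day 0 biomarker measurements (Table 2").

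**The concern.** A between-arm comparison at a timepoint is protected by randomization when both arms are measured at the same time after randomization. The third sample does not meet that condition. A child who recovers quickly is sampled shortly before an early discharge, a child with a long stay on day 27, and a dying child before death. If fluid type changes time to discharge or the risk of death, the arms are sampled at different stages of illness. The contrast then mixes a biomarker effect with a difference in sampling time. Percent change from day 0 to the last sample has the same fault, because only its starting point is fixed.

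The mechanistic reading of the trial is at stake. The Outcomes section presents kidney injury as the main pathway by which balanced fluid would help. A last-sample result distorted by timing could appear to contradict, or to support, the clinical result for reasons unrelated to injury.

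A smaller question arises at the other end of the schedule. Day 0 is defined only as a calendar day, and its value serves both as the reference for percent change and as a subgroup factor.

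**Working it through.** **1. Is there a figure to reproduce?** The article gives no biomarker sample size, SD, effect size or rate of decline, so no stated figure is in dispute. The nearby power statements, which concern the events that set the last sampling time, are consistent:

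- Mortality 3% versus 2% with 4,400 per arm gives power of 83.9% at two-sided alpha 0.044 and 85.2% at 0.05 (stated: 84%).
- Power above 99% for 1 hospital-free day requires an SD below 1 / [√(2/4400) × (1.960 + 2.326)] ≈ 10.9 days. The article gives no SD.

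**2. Which contrasts depend on a post-randomization time?**

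| Contrast | Sampling time | Depends on discharge or death? |
|---|---|---|
| Day 2, absolute | Fixed day | No, apart from children who die or leave before day 2 |
| Day 2, percent change | Fixed day, day-0 reference | As above; also depends on when the day-0 sample was taken |
| Last sample, absolute | Day 27, or earlier at discharge or death | Yes |
| Last sample, percent change | As above, day-0 reference | Yes |

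The intervention window closes at the end of the calendar day after randomization (day 1), so day 2 is the first day after it.

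**3. How large could the timing effect be?** This is an illustration. None of its inputs is a biomarker figure from the documents. Suppose both arms share one trajectory that falls log-linearly to zero with half-life h days, and one arm is sampled d days earlier. With no true biomarker effect, the ratio of last-sample values (earlier arm over later arm) is 2^(d/h).

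| Half-life h (assumed) | d = 0.5 day | d = 1 day |
|---|---|---|
| 2 days | 1.19 | 1.41 |
| 3 days | 1.12 | 1.26 |
| 5 days | 1.07 | 1.15 |
| 7 days | 1.05 | 1.10 |

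If the day-0 values are balanced, the ratio of fold-changes from day 0 carries the same factor.

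The 1-day column is not a forecast. One hospital-free day appears in the article as a detectable difference, and that outcome combines death with discharge. The 3% versus 2% mortality difference alone could contribute up to 1% × 28 = 0.28 day.

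**4. The day-0 reference.** Study fluid starts at randomization, enrollment may precede consent, and biomarkers need separate written consent. The article therefore permits a day-0 sample taken after study fluid has begun, but it does not say that this happens. If a share f of a true day-2 ratio R were already present at day 0, the ratio of fold-changes would be R^(1−f). With R = 0.80 (assumed):

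- f = 10% gives 0.82.
- f = 25% gives 0.85.
- f = 50% gives 0.89.

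**The case against.** **The last sample may be a deliberate end-of-stay measure.** It parallels MAKE30, which is assessed at 30 days or at hospital discharge if that is earlier, and it suits a pragmatic trial with limited data collection. This stands as a reason to keep the sample. It does not justify comparing arms on it as a single timepoint.

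**The plan already contains a sound contrast.** The day-2 absolute comparison uses a fixed day and needs no baseline. This stands. A reader might infer that the whole biologic aim rests on treatment-dependent times and a treated baseline. The documents do not support that.

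**The size and direction are not established.** This also stands. The half-lives are assumed, and a marker that settles at a non-zero level gives a smaller ratio. If children leave sooner because they recover faster, the trajectories differ between arms as well. It is tempting to say that the arm discharged sooner must look worse, but that follows only under the identical-trajectory assumption.

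**The day-0 point rests on silence.** The full protocol or a laboratory manual may fix the order of sampling and fluid, and the secondary-outcome analysis is in Additional file 4; none of these is shown. This stands, so the point is only a check. Restricting all baselines to samples taken before study fluid would also lose an unknown share of a subset-of-sites sample and would select on early collection. Even those samples need not be untreated, because eligibility allows up to 40 mL/kg of earlier crystalloid.

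**Conclusion.** The concern holds for the last biomarker sample. As written, its absolute and percent-change contrasts compare the arms at child-specific times set by discharge or death, and both events may depend on fluid type. The conclusion follows from the stated schedule and the stated contrasts and needs no assumed number. The direction and size of the bias cannot be determined from the documents. The range of about 1.05 to 1.41 is an illustration that rests on assumed half-lives of 2 to 7 days, decay to zero, one shared trajectory and a 0.5 to 1 day shift in sampling.

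The reach is limited. The day-2 absolute comparison is largely unaffected, apart from children who die or leave before day 2. The primary outcome is unaffected. That the day-0 baseline is already treated is only a possibility; it would bear on the day-0 values themselves, on percent change and on the day-0 biomarker subgroup.

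**What to change.** 1. Name day 2, the fixed day just after the intervention window closes, as the main biologic contrast.
2. Label the third sample an end-of-stay value. Either analyze it in a longitudinal model using actual time since randomization, or report it as supportive only.
3. Use recorded collection times to run a sensitivity analysis, limited to day-0 samples taken before study fluid, of percent change and of the day-0 biomarker subgroup. Keep the other baselines in the main analysis. If the full protocol already places the sample before study fluid, one sentence saying so is enough.

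The cost is slightly more analysis work and a weaker claim from the last sample. No new samples are needed. The restricted sensitivity analysis will be smaller and selected on early collection, and should be read with that in mind.
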